## Abstract

**Background:**

Chronic lung diseases (CLDs) such as chronic obstructive pulmonary disease, interstitial lung disease, and chronic asthma contribute significantly to the global burden of disease. Pulmonary rehabilitation (PR) is an effective intervention for improving the exercise capacity, increasing the quality of life, and reducing hospitalizations in individuals with CLD. However, benefits from PR quickly decline following discharge from traditional programs. Telerehabilitation (tele-rehab) has emerged as a potential solution for extending the benefits of PR; yet, few studies have compared its efficacy with conventional onsite maintenance rehabilitation.

**Objective:**

This pilot protocol aims to assess the effectiveness of an 8-week supervised maintenance rehabilitation program delivered onsite or remotely via tele-rehab in patients with CLD.

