**Methods:**

This randomized, assessor-blinded feasibility pilot trial will enroll 30 participants who have completed outpatient PR. Participants will be randomized into 2 groups: (1) tele-rehab, involving remotely supervised sessions conducted via videoconferencing or (2) onsite maintenance rehabilitation with in-person sessions. Both groups will receive weekly supervised sessions for 8 weeks facilitated by licensed physical therapists. Assessments will be conducted onsite at baseline, after the 8-week intervention, and at 1-month follow-up by a blinded assessor. The feasibility of the intervention and the study methods will be assessed by the log-in into the number of sessions attended after randomization, the ease of using the equipment and procedures, optimal session length, and adherence to the intervention protocol. Clinical outcomes will include dyspnea and perceived exertion, respiratory muscle strength, physical function, 6-minute walk distance, physical activity, and quality of life. Descriptive statistics with means and standard deviations for continuous and frequency distributions for categorical data will be utilized to report individual and group characteristics. Feasibility outcomes will be compared using independent 2-sided *t* tests. Between-group comparisons will use mixed analysis of variance, and within-group comparisons will be analyzed with a repeated measures analysis of variance.

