**Conclusions:**

This study hypothesizes that both tele-rehab and onsite programs will significantly improve clinical outcomes, with tele-rehab yielding comparable benefits to onsite maintenance. Findings will provide evidence supporting accessible and sustainable maintenance rehabilitation options for patients with CLD and guide future large-scale efficacy trials.

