Despite strong evidence demonstrating PR effectiveness, reported benefits rapidly decline after discharge in the absence of supervised maintenance as adherence to health-enhancing behaviors and physical activity levels wane over time [10,11]. To promote long-term adherence, patients may need a continuum of care with tapered supervision beyond formal PR. Supervised maintenance programs involve ongoing supervised exercise at a lower frequency than PR programs. Although an abundance of literature supports the benefits of PR, studies examining maintenance programs are scarce and demonstrate mixed results. Limited studies using community-based supervised maintenance following PR have demonstrated a strong potential of these programs in maintaining a variety of outcomes, including physical activity level, quality of life, 6-minute walk distance, and dyspnea scores [12], but other studies on maintenance have failed to demonstrate these benefits [13,14]. Overall, the certainty of evidence on the benefits of maintenance programs is deemed low, particularly due to inconsistent performance on outcome measures, high risk of bias, lack of rigorous methodologies, attrition, and small sample sizes [15]. Ongoing improvements in outcomes are believed to result from enhanced function, exercise tolerance, and symptom control with structured maintenance programs [6,7,15]. However, access barriers and adherence challenges persist, highlighting the need for feasible, scalable models like telehealth [16]. These limitations underscore the need for well-designed studies to evaluate the feasibility and effectiveness of supervised maintenance programs, particularly those delivered via telehealth.

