### Study Design

This study follows the CONSORT (Consolidated Standards of Reporting Trials; Multimedia Appendix 1) and SPIRIT (Standard Protocol Items: Recommendations for Interventional Trials; Multimedia Appendix 2) guidelines. The study will be a randomized, assessor-blinded, pilot feasibility trial. Participants will be randomly assigned in a 1:1 allocation ratio to either (1) a tele-rehab group with remotely supervised intervention or (2) an onsite group with in-person supervision. Figure 1 outlines the study design and recruitment process. The anticipated study period is from September 1, 2023, to April 1, 2026.

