### Statistical Analysis

Since a large 2-group comparative study has not yet been published, this pilot study will generate an estimate of variance and the percentage of change in outcomes needed to determine the power and sample size for a larger study. Therefore, estimation rather than statistical testing is the main objective of this study. Given the possibility of attrition from dropouts, we will recruit 40 participants with a goal to have 30 participants complete the study (15 in each group). Descriptive statistics will be used to summarize the demographic and clinical characteristics and outcomes for all the participants. Feasibility will be assessed using frequency distributions of session adherence and use of activity logs. Comparisons between groups on all outcomes at preintervention and postintervention will be conducted with the intention to treat using a mixed analysis of variance. Within-group comparisons at all 3 time points will be conducted via a repeated measures analysis of variance. Adherence to the program between groups will be compared using independent 2-sided *t* tests. Finally, descriptive statistics with frequency distributions of adverse events, planned and unplanned physician visits, and frequency of use of daily activity log will be reported.

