### Conclusions

This pilot randomized feasibility trial aims to address critical gaps in the long-term management of CLD by comparing onsite and tele-rehab supervised maintenance programs. The study emphasizes the importance of overcoming traditional barriers to PR, such as transportation challenges and limited facility availability while promoting equitable access to care. By focusing on improving self-efficacy and adherence to health-enhancing behaviors, this intervention has the potential to sustain the benefits of PR beyond discharge and reduce adverse health outcomes. The trial will provide valuable data on feasibility, adherence, and clinical outcomes for tele-rehab and onsite programs, providing insights for the development of larger-scale trials. Additionally, this study addresses the growing need for innovative care models that incorporate technology to enhance patient outcomes and reduce health care disparities. Despite the acknowledged limitations such as the small sample size, language restrictions, and the potential for dropout, the findings will contribute valuable information to guide future efficacy trials. This trial has the potential to inform future standards of care for patients with CLD by demonstrating the feasibility of accessible and effective tele-rehabilitation maintenance programs to sustain long-term health benefits.

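### Abstract objective and hypothesis claim an absolute program effect that two active maintenance arms cannot identify

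*Protocol article*

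**What the plan says.** The design has two active arms. Study Design states: "Participants will be randomly assigned in a 1:1 allocation ratio to either (1) a tele-rehab group with remotely supervised intervention or (2) an onsite group". The abstract's Methods add: "Both groups will receive weekly supervised sessions for 8 weeks facilitated by licensed physical therapists". The Tele-Rehab Group section gives that arm the onsite protocol, with only the mode of aerobic exercise adapted to available equipment. The article describes no arm without maintenance and no external benchmark.

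The wording about effect differs from place to place:

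- Abstract, Objective: the pilot "aims to assess the effectiveness of an 8-week supervised maintenance rehabilitation program delivered onsite or remotely".
- Abstract, Conclusions: the hypothesis is that "both tele-rehab and onsite programs will significantly improve clinical outcomes", with tele-rehab giving similar benefit to onsite.
- Introduction, last paragraph: two numbered aims, namely feasibility of tele-rehab relative to onsite and a comparison of the two modes on clinical outcomes. The hypothesis after them presumes that both arms improve.
- Discussion, Overview: the trial is described as examining the effectiveness of virtually delivered maintenance.
- Discussion, Conclusions: the trial could inform later standards of care "by demonstrating the feasibility of accessible and effective tele-rehabilitation maintenance programs to sustain long-term health benefits".

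Statistical Analysis makes estimation, not testing, the main objective. It plans a mixed analysis of variance between groups and adds: "Within-group comparisons at all 3 time points will be conducted via a repeated measures analysis of variance".

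**The concern.** The abstract objective and hypothesis are about whether maintenance works. The randomized comparison is about whether it works differently by delivery mode. Whatever both arms share, including the whole program effect if the modes are equally good, cancels out of that comparison. The only planned analysis left that bears on improvement in both arms is the within-group repeated measures analysis. It has no concurrent control, so it combines any program effect with familiarity on the walk and chair tests, regression to the mean and the natural course of the disease.

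The article's own background makes this sharper in two ways. First, the Introduction says that gains from rehabilitation fall away quickly without supervised maintenance, so the right reference for a maintenance program is decline rather than no change. Second, onsite maintenance cannot serve as a proven reference treatment, because "the certainty of evidence on the benefits of maintenance programs is deemed low" and some studies of it showed no benefit. Two similar arms are then equally compatible with both programs working and with neither working.

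At stake is what the trial may conclude. Read against the abstract's hypothesis, a within-arm rise could be taken as evidence of effectiveness and carried into the larger trial, while a program that truly held off decline could be judged to have failed.

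**Working it through.** **1. The plan's own figure.** Statistical Analysis recruits 40 so that 30 complete, 15 per arm. The implied dropout is 1 − 30/40 = 25%, and 30/(1 − 0.25) = 40, so the figures agree. The article gives no alpha, power, effect size, SD or margin, so there is no power calculation to reproduce.

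**2. What each analysis identifies.** Let C be the mean change that would occur without the program (natural course, retest familiarity, regression to the mean) and P the program effect.

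- Within an arm, the expected change is C + P.
- Between arms, randomization makes C equal in expectation, so the difference is (C + P_tele) − (C + P_onsite) = P_tele − P_onsite.

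Neither quantity isolates P. With assumed values in SD of change, and P the same in both arms:

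| Case | C | P | Within-arm change | Between-arm difference |
|---|---|---|---|---|
| Ineffective program, retest gain | +0.5 | 0 | +0.5 | 0 |
| Program fully prevents decline | −0.5 | +0.5 | 0 | 0 |
| Ineffective program, no shift | 0 | 0 | 0 | 0 |

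The ineffective program in the first row looks successful. The fully effective program in the second row looks the same as the ineffective one in the third.

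**3. How often a non-treatment gain would look like improvement.** Inputs: n = 15 completers per arm (Statistical Analysis); P = 0; a non-treatment gain d in SD of change (assumed); a paired t test at two-sided 5%, counting improvement only, as a simplification of the three-visit analysis of variance.

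One arm: probability = Pr(T > t₀.₉₇₅,₁₄ = 2.145), where T is noncentral t with 14 degrees of freedom and noncentrality d√15. Both arms, taken as independent with the same gain: the square of that probability.

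| d (assumed) | d√15 | One arm | Both arms |
|---|---|---|---|
| 0 | 0 | 2.5% | 0.06% |
| 0.3 | 1.16 | 19% | 4% |
| 0.5 | 1.94 | 44% | 19% |
| 0.8 | 3.10 | 82% | 67% |

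The both-arms column is the closer match to the abstract's hypothesis, which concerns both programs. The d = 0 row also applies to a program that exactly offsets decline: it would show significant improvement in an arm only 2.5% of the time.

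**4. Whether the between-arm result could fill the gap.** With 15 per arm, the 95% confidence interval for a difference in means has half-width t₀.₉₇₅,₂₈ × √(2/15) = 2.048 × 0.365 = 0.75 SD. Even a point estimate of zero would leave differences of up to about 0.75 SD open in either direction, and it would still say nothing about P itself.

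**5. Whether adding an untreated arm at this size would help.** Assume a 0.5 SD difference from no maintenance and two-sided 5%. Power with 15 per arm is Φ(0.5/√(2/15) − 1.96) = Φ(1.37 − 1.96) = 28%. For 80% power, n = 2(1.96 + 0.84)²/0.5², which rounds up to 63 per arm. A third arm at pilot size would not establish effectiveness.

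**The case against.** The strongest reply is that the article already frames the trial properly where it matters. The Introduction's numbered aims are feasibility and a comparison of the two modes, the abstract's Results section is also comparative, and Statistical Analysis puts estimation ahead of testing. Limitations concedes low power for efficacy, and the abstract defers efficacy to later large trials. On this view the abstract objective is only a one-sentence condensation.

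Much of that stands. Two active arms suit the numbered aims and the estimation aim, and neither needs to change. But the abstract objective and hypothesis are not shortened forms of those aims; they assert something different. The concession in Limitations is about power, which more patients would cure. No number of patients in these two arms supplies the missing comparator, and Limitations does not mention it. Nor is this a detail that an analysis plan could settle, because no analysis of two active arms isolates the effect of maintenance itself.

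Four stronger readings are tempting but not supported:

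- *A reader might infer that the protocol will declare effectiveness from a significant within-arm test.* No sentence says so. The link follows only because that is the one planned analysis bearing on the hypothesis.
- *A reader might infer that the Discussion's Conclusions section claims proven effectiveness.* The sentence is hedged, and what it says will be demonstrated is feasibility.
- *A reader might infer that false improvement is likely.* The gains in the illustration are assumed, and the only course the article describes without maintenance is decline, which works against a spurious rise.
- *A reader might add a count of false positives over many outcomes and both arms.* That is a separate multiplicity matter and does not bear on the missing comparator.

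**Conclusion.** The point holds in a limited form. The abstract's objective and hypothesis, repeated in the Discussion overview and presumed in the Introduction's hypothesis, state an absolute program effect that this design cannot identify. Uncontrolled within-arm change can mislead in either direction: it can credit an ineffective program with retest gains, or miss a program that prevents decline.

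The structural part rests only on the stated arms and analyses and needs no assumption about size. The percentages are illustrative. They assume 15 completers per arm, no program effect, shifts of 0.3 to 0.8 SD of change, a simplified paired test and, for the both-arms figures, independent arms. A reader might conclude that the two-arm design is itself wrong or that an untreated arm is required. The documents do not support that: the design fits the numbered aims and the estimation aim, and the fault lies in the wording and in the role given to within-arm testing.

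**What to change.** Keep both arms and change the following:

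- **Abstract, Objective and Conclusions; Discussion, Overview:** restate the purpose as feasibility and the estimated tele-rehab minus onsite difference with its confidence interval. Remove the hypothesis of significant improvement in both programs.
- **Introduction, final hypothesis:** drop the presumption that both arms improve. Leave the two numbered aims as they are.
- **Statistical Analysis:** report within-arm change descriptively, as mean change with confidence interval at each visit, and not as a significance test of effectiveness. This agrees with the section's own estimation aim.
- **Limitations:** state that there is no comparator without maintenance, so the trial cannot show that either program is effective or preserves the gains from rehabilitation, whatever its size.
- **Discussion, Conclusions:** confine the closing claim to feasibility.

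The article says that analysis starts by April 30, 2026, so the same wording can be carried into the analysis plan and the results paper before the outcomes are interpreted. The change adds no patients, visits or procedures and leaves the sample size alone. Its only price is a more modest claim.

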**Methods:**

This randomized, assessor-blinded feasibility pilot trial will enroll 30 participants who have completed outpatient PR. Participants will be randomized into 2 groups: (1) tele-rehab, involving remotely supervised sessions conducted via videoconferencing or (2) onsite maintenance rehabilitation with in-person sessions. Both groups will receive weekly supervised sessions for 8 weeks facilitated by licensed physical therapists. Assessments will be conducted onsite at baseline, after the 8-week intervention, and at 1-month follow-up by a blinded assessor. The feasibility of the intervention and the study methods will be assessed by the log-in into the number of sessions attended after randomization, the ease of using the equipment and procedures, optimal session length, and adherence to the intervention protocol. Clinical outcomes will include dyspnea and perceived exertion, respiratory muscle strength, physical function, 6-minute walk distance, physical activity, and quality of life. Descriptive statistics with means and standard deviations for continuous and frequency distributions for categorical data will be utilized to report individual and group characteristics. Feasibility outcomes will be compared using independent 2-sided *t* tests. Between-group comparisons will use mixed analysis of variance, and within-group comparisons will be analyzed with a repeated measures analysis of variance.

**Results:**

Recruitment for this institutional review board—approved study (approval date: July 25, 2023) began in January 2024, with 11 (37%) of the 30 participants enrolled to date. This study will generate data comparing tele-rehab and onsite rehabilitation in terms of the primary and secondary outcomes. Use data such as program adherence and attrition will also be reported. The results will inform the feasibility, adherence, and effectiveness of tele-rehab as a sustainable alternative to onsite maintenance rehabilitation. The study is anticipated to be completed by April 2026.

**Conclusions:**

This study hypothesizes that both tele-rehab and onsite programs will significantly improve clinical outcomes, with tele-rehab yielding comparable benefits to onsite maintenance. Findings will provide evidence supporting accessible and sustainable maintenance rehabilitation options for patients with CLD and guide future large-scale efficacy trials.

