One method to improve adherence in maintenance programs is telerehabilitation (tele-rehab), which is a way of participating in medical appointments via a technology device [17]. Tele-rehab is a viable alternative rehabilitation approach for patients with CLD and holds potential as an effective tool for increasing positive behavioral changes, including long-term adherence and a more physically active lifestyle [18-21]. Few studies [18,22-24] have compared the benefits of tele-rehab versus onsite PR on health outcomes in people living with CLD, and even fewer studies have compared supervised maintenance programs delivered via tele-rehab with onsite maintenance, leaving many gaps in the literature [25]. Furthermore, most studies are limited to people with COPD, with only a small number investigating the effects of tele-rehab on other CLDs [26,27].

Given these limitations, there is a clear need for well-designed feasibility studies to evaluate the effectiveness and practicality of supervised maintenance programs, particularly those delivered via telehealth. The purpose of this pilot feasibility trial is to (1) assess the feasibility of delivering an 8-week supervised maintenance program remotely via tele-rehab in comparison to onsite delivery and (2) compare the effectiveness of these interventions on clinical outcomes in patients with CLD. We hypothesize that tele-rehab will be feasible to implement, with acceptable adherence, and will yield comparable improvements in clinical outcomes to onsite rehabilitation.

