### Limitations

There are several limitations that we would like to acknowledge. Although we anticipate achieving a feasible, acceptable, and high-fidelity protocol, it is possible that some challenges remain. Given a feasibility pilot, we anticipate being underpowered to assess intervention efficacy. Despite the randomized design, allocation concealment is not possible. The risk of participants dropping out after learning their allocation assignment cannot be ruled out. We have taken measures to minimize this risk by having trained research staff instead of staff manage action planning and SMS text messaging procedures to avoid any accidental information exchange about other participants. Although steps are taken to improve access to all potential individuals, limiting inclusion to participants who speak English may limit the reach to participants who have limited English proficiency.

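### The article hypothesises comparable benefit but names only difference tests, with no margin and 15 completers per arm, so the pilot can estimate the difference but cannot show comparability

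*Protocol article*

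**What the plan says.** The expectation appears in two places. The Conclusions of the Abstract read: "This study hypothesizes that both tele-rehab and onsite programs will significantly improve clinical outcomes, with tele-rehab yielding comparable benefits to onsite maintenance". The last paragraph of the Introduction expects that tele-rehab "will yield comparable improvements in clinical outcomes to onsite rehabilitation". The Objective in the Abstract says that the pilot "aims to assess the effectiveness of an 8-week supervised maintenance rehabilitation program".

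For the analysis, the Statistical Analysis section says: "Comparisons between groups on all outcomes at preintervention and postintervention will be conducted with the intention to treat using a mixed analysis of variance". Change within each arm over the three time points is tested by repeated-measures ANOVA. The Methods paragraph of the Abstract names the same two analyses. Nothing in the article gives a margin, a significance level, an SD or a meaning for comparable. The Statistical Analysis section plans to recruit 40 so that 30 complete, 15 per arm, whereas the Abstract gives 30 as the number to enrol.

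The same section also states that "estimation rather than statistical testing is the main objective of this study", and Limitations adds: "we anticipate being underpowered to assess intervention efficacy".

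**The concern.** The hypothesis and the analysis do not match. A mixed ANOVA asks whether the arms differ. Failing to detect a difference is not evidence that the difference is small, and in a trial of this size it is weak evidence of anything. To support comparability one needs an interval for the difference and a statement of how large a difference would still be acceptable. The article names neither.

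The text also pulls in two directions. It declares estimation as the aim and expects low power, yet it keeps an effectiveness objective, hypothesises significant improvement, and describes the comparisons as tests. A non-significant ANOVA is a likely output when the true deficit is small or moderate, and it is the only named between-arm result that bears on the hypothesis. It could therefore be taken as confirmation.

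The expected significant improvement in both arms has a related weakness. Both arms receive weekly supervised sessions and there is no unsupervised arm, so change from baseline within an arm cannot be separated from the natural course, test familiarity or regression to the mean. The Introduction says that benefits fade after rehabilitation ends, so holding steady may already be a success for a maintenance programme. A significance test for improvement does not address that.

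**Working it through.** **Inputs from the article.** 1:1 allocation (Study Design); 15 completers per arm, 40 recruited, intention to treat (Statistical Analysis).

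**Assumed, because the article does not give them.** Two-sided alpha 0.05; true deficits in SD units; pre-post correlation ρ from 0.5 to 0.9.

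**The plan's own figure.** There is no power calculation to reproduce. Moving from 30 completers to 40 recruits implies 1 − 30/40 = 25% attrition, and 30/(1 − 0.25) = 40. This checks the arithmetic only, since the 25% is derived from the same two numbers. The analysed number could be 15 per arm (completers) or up to 20 per arm (all 40), so both are shown.

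**1. Chance of a non-significant between-arm test.** Two-sample t test with non-centrality d·√(n/2). At d = 0.5:
- n = 15: 0.5 × √7.5 = 1.37 on 28 df, power 0.262, non-significant 74%.
- n = 20: 0.5 × √10 = 1.58 on 38 df, power 0.338, non-significant 66%.

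| True deficit (SD of analysed variable) | 15 per arm | 20 per arm |
|---|---|---|
| 0.3 | 88% | 85% |
| 0.5 | 74% | 66% |
| 0.8 | 44% | 31% |
| 1.0 | 25% | 13% |

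The chance falls to 50% at 0.74 SD (15 per arm) or 0.64 SD (20 per arm). Power of 80% needs 1.06 SD or 0.91 SD.

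**2. Allowing for the pre-post design.** With two time points, the group-by-time test in a mixed ANOVA is a t test on change. A deficit of d baseline SDs becomes d/√(2(1 − ρ)) SDs of change. For d = 0.5 and 15 per arm:

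| ρ | Deficit in SDs of change | Non-significant |
|---|---|---|
| 0.5 | 0.50 | 74% |
| 0.7 | 0.65 | 60% |
| 0.8 | 0.79 | 45% |
| 0.9 | 1.12 | 16% |

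**3. Precision.** The 95% CI half-width is t × √(2/n), in SDs of the analysed variable:
- n = 15: 2.048 × √(2/15) = 0.748.
- n = 20: 2.024 × √(2/20) = 0.640.

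**4. What a margin-based test would need.** Non-inferiority with one-sided alpha 0.025, 80% power, true difference zero and an assumed margin of 0.5 SD: n = 2(1.960 + 0.842)²/0.5² = 62.8, so 63 per arm. With 15 per arm the power is Φ(0.5/√(2/15) − 1.960) = Φ(−0.59) = 28%.

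**The case against.** The strongest reply is that comparability appears only as a hypothesis. The article says openly that estimation is the aim, that power is low, and that the results are meant for a larger trial. A condensed article may also leave the reporting of confidence intervals to an analysis plan that is not shown. Much of this stands, and it rules out several stronger readings that a reader might infer.

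- *The investigators intend to declare comparability from a non-significant ANOVA.* No section writes such a rule.
- *A truly inferior tele-rehab arm would most likely be reported as comparable.* The article does not support this as a general statement. Non-significance is the more likely outcome only for deficits below 0.74 SD at 15 per arm (0.64 SD at 20), or below smaller values in baseline SDs if the pre-post correlation is high. Being non-significant is also not the same as being reported as comparable.
- *Testing 13 clinical measures gives about a 49% chance of a false positive* (1 − 0.95¹³ = 0.487). That count includes three measures that the article lists as baseline vitals; without them 1 − 0.95¹⁰ = 0.401. Both figures assume independence, which is implausible for several walking and chair-rise tests. Handling of multiplicity in a pilot may also sit in the analysis plan.
- *The pilot should itself run a margin-based test.* At this size such a test would usually fail even if the arms were identical.

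The reply does not remove the mismatch. The article commits to a comparability hypothesis and names no analysis that could bear it out. The declared estimation aim is a reason to bring the hypothesis and objective into line with it.

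**Conclusion.** The point holds as a mismatch between hypothesis and analysis, and this does not depend on any assumed number. With no margin and only difference tests named, comparability cannot be supported, and within-arm change cannot be credited to either programme.

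The size of the risk of misreading does rest on assumptions. At two-sided alpha 0.05, a true deficit of 0.5 SD of the analysed variable would be non-significant about three times in four at 15 per arm and two times in three at 20. In baseline SDs the risk at 15 per arm could be as low as 16% if the pre-post correlation is 0.9. An interval of about ±0.75 SD (±0.64 SD at 20 per arm) around an observed difference of zero would still leave a deficit of 0.5 SD open.

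**What to change.** 1. In Statistical Analysis, make the tele-minus-onsite difference with its 95% CI the main result for each clinical outcome.
2. State there that a non-significant ANOVA will not be read as evidence of comparability.
3. Reword the Objective and Conclusions of the Abstract and the aims and hypothesis in the Introduction, so that they speak of estimating the difference and its variance and no longer of effectiveness, significant improvement or comparability.
4. Report within-arm change descriptively with CIs, without attributing it to the programme.
5. Leave any margin-based test to the larger trial (about 63 per arm for a 0.5 SD margin under the assumptions above). If the word comparable is kept, fix and justify a margin before the analysis, which Results says will start by April 30, 2026. Allow the word only if the CI excludes that margin, and otherwise report the result as inconclusive. Results already contrasts walk-test scores by arm for one participant in each, so the margin should be justified without reference to those data.
6. Reconcile the 30 enrolled in the Abstract with the 40 recruited in Statistical Analysis, because this sets whether 15 or 20 per arm are analysed.

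The cost is wording only; no participant, visit or measurement changes. The downside is that the pilot gives up the conclusion that tele-rehab is comparable and will probably be inconclusive on clinical outcomes.
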